#### 2.1.2. Exclusion criteria.

Participants that will be excluded from the study:

With a history of photosensitivity.Who has any type of lesion on the skin on the face.Who use corticosteroids, anticoagulants, or any drug known to increase photosensitivity, including systemic retinoids and use of topical retinoic acid in the last 6 months.People with any collagen-related diseases, malnutrition, anemia, immunosuppression, cancer diseases, smokers, predisposition to hypertrophic and keloid scarring, history of dermatological diseases, surgery on the face, trauma on the face, diseases that could affect the condition of the skin, and psychiatric disease.Who are in the menstrual period, in the climacteric, or in hormone replacement therapy.Who underwent cosmetic procedures on the face, such as application of botulinum toxin in the last 8 months, facial filling in the last year, chemical peels, ablative LASER, and dermabrasion in the last 6 months.Who does not respect the post-treatment recommendations or fails to attend a treatment session.Patients who present an adverse event (hypersensitivity, allergies) will not be part of the statistical analysis. However, these data will be described and discussed, as well as the possible adverse effects and the participants will receive treatment to resolve the condition. These data will be described and treated according to the complication.

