#### 2.1.3. Sample size calculation.

The sample size was calculated based on the primary outcome. The outcome considered was the classification of the Lemperle Wrinkle Assessment Scale (WAS).^[29]^ In the study by Sylvie Boisnic,^[30]^ the authors observed that the Lemperle score decreased in both groups after 12 weeks of treatment with a reduction of 1 (±0.7) point in the experimental group and 0.34 (±0.5) point in the placebo group and a statistically significant (*P* < .0002) change from baseline between the 2 groups after 8 weeks of treatment. This study was designed to detect a difference in scores between the groups, considering the mean and standard deviation of the study by Sylvie Boisnic,^[30]^ for the analysis of variance (ANOVA) with 3 groups and repeated measures, with significance level of 5% and power of 95%, with equal allocation for the three groups, requiring 24 participants per group, 72 in total. To control a possible loss, 50% can be added to the sample, with 36 participants per group, that is, 108 in total. The sample calculation was performed using the G-Power Version 3.1.9.4 program (Universität Kiel, Germany).

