#### 2.1.4. Randomization.

After completing a questionnaire and being evaluated by the researcher for inclusion and exclusion criteria, a person not involved in the study will randomly distribute the participants among the three experimental groups using an online random sequence generator program (https://www.randomizer.org/tutorial/). After this, opaque envelopes, containing the generated number, will be sealed and will remain in a safe place until participants are recruited for the outpatient clinic. When the participant enters the clinic, the researcher will open the corresponding envelope and begin the specified treatment. Participants will be divided into 3 groups:

(Group 1) Application of PBM twice a week for 4 weeks;

(Group 2) Application of PBM three times a week for 4 weeks;

(Group 3) Application of simulated PBM twice a week for 4 weeks;

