#### 2.1.6. Interventions.

The participants will be instructed not to use any cream with an active element for 2 months. All of them will receive a bottle of neutral hydrating cream for daily use in the morning and before bed. The cream formulation is composed of carbomer, cetearyl alcohol, glyceryl stearate/polyethylene glycol-100 stearate, helianthus annuus seed oil, butylated hydroxytoluene, disodium ethylenediaminetetraacetic acid, glycerin, propylene glycol, aminomethyl propanol, phenoxyethanol, ethylparaben, butylparaben, propylparaben, isobutylparaben, and aqua.

Each participant will have their face cleaned with a neutral nonalcoholic wet wipe and their eyes blindfolded and protected with goggles that allow the rest of the face to be illuminated with the red LED or with simulated light without the participant knowing which treatment was applied. A transparent plastic film will be used to cover the face before placing the LED mask, material supplied by the same manufacturer of the mask.

The equipment used will be LED masks (Cicatrillux Bio next from Cosmedical, Mauá, São Paulo—SP, Brazil) (Fig. 2), containing 92 LEDs with red wavelength (660 ± 10 nm) in the parameters described in Table 1. The application time will be 21 minutes per session, totaling 3 cycles of 7 sequential minutes due to the device’s shutdown time. The LED mask will be applied 3 times a week for 4 weeks in patients in group 1 and twice a week for 4 weeks in patients in group 2. In participants in group 3, the mask will be kept off and a white light next to the stretcher will be turned on for the participants to have the sensation of luminosity. The same beep will be emitted each cycle and the participants received the simulated application twice a week for 4 weeks.

**Table 1 T1:** LED device dosimetric parameters. Pg 10.

Parameters	Red LED
Wavelength (nm)	660 (±10 nm)
Spectral bandwidth (nm)	20
Operation mode	Continuous
The radiant power of each LED (mW)	5.02
Polarization	Random
Opening diameter of each LED (mm)	10
Irradiance at the opening of each LED (mW/cm^2^)	6.4
Beam area on target (cm^2^)	0.785
Application time (min)	21
Radiant LED exposure (J/cm^2^)	8.02
Radiant energy by LED (J)	6.3
Light emission angle	90º
Application mode	Contact
Anatomical location of application points	Face

LED = light emitting diode.

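### Excluding participants after allocation for a missed session, non-adherence or a reaction removes the protection of randomisation, and is expected to fall hardest on the 12-session arm

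*Protocol article*

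**What the plan says.** Section 2.1.2 (Exclusion criteria) mixes baseline criteria with events that arise during treatment. One item excludes from the study anyone "Who does not respect the post-treatment recommendations or fails to attend a treatment session". The last item reads "Patients who present an adverse event (hypersensitivity, allergies) will not be part of the statistical analysis", and adds that such cases will be described, discussed and treated.

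Section 2.1.4 (Randomization) sets the order. Eligibility is checked, the participant is allocated, and then: "When the participant enters the clinic, the researcher will open the corresponding envelope and begin the specified treatment". The arms are "Group 1) Application of PBM twice a week for 4 weeks", "Group 2) Application of PBM three times a week for 4 weeks" and "Group 3) Application of simulated PBM twice a week for 4 weeks". Section 2.1.6 (Interventions) says of sham: "In participants in group 3, the mask will be kept off and a white light next to the stretcher will be turned on". It also gives every participant the same cream, wipe and plastic film. Section 2.2.2 adds a silicone impression of the forehead in all arms.

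Section 2.1.3 requires 24 per group and provides a reserve: "To control a possible loss, 50% can be added to the sample, with 36 participants per group". Section 2.3 plans repeated measures ANOVA with Tukey comparisons and says nothing that returns the excluded participants to the analysis.

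**The concern.** A missed session, a breach of advice given after treatment, or a reaction to treatment can only follow allocation. Removing participants for these reasons replaces the randomised groups with groups selected on what happened under treatment.

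The removal is also tied to the treatments. A single missed session is enough for exclusion, and the arms do not have the same number of sessions to miss. Reactions to the red LED can arise only where the LED is on, so participants who tolerated it badly leave the efficacy comparison in the active arms. The trial exists to compare application frequencies, and the attendance rule selects on frequency itself. A difference between regimens could be created or hidden by who remains. Recruiting more participants restores numbers but does not undo the selection.

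**Working it through.** **The plan's own figures.** Section 2.1.3 gives changes of 1 (SD 0.7) and 0.34 (SD 0.5).
- Difference: 1 − 0.34 = 0.66.
- Pooled SD: √((0.49 + 0.25)/2) = 0.608.
- Standardised difference: 0.66/0.608 = 1.085.
- At two-sided 5% and 95% power, the normal approximation gives 23 per arm. The exact t calculation gives 24 (power 0.957; 0.949 at 23).
- Reserve: 24 × 1.5 = 36 per group.

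The article does not give its repeated-measures inputs, but a two-group t test on change reproduces 24. The reserve covers a loss of at most 1 − 24/36 = 33.3% per arm.

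**Sessions.** From section 2.1.4: 2 × 4 = 8 (PBM twice weekly), 3 × 4 = 12 (PBM three times weekly), 2 × 4 = 8 (sham). Section 2.1.6 swaps the regimens of groups 1 and 2. The two sections must be reconciled, but either way one active arm has 12 sessions, and the other active arm and sham have 8.

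**Expected loss under the attendance rule.** The article states no attendance rate. Let p be an assumed chance of missing any one session, independent between sessions, equal across arms, with no rescheduling. The share excluded is 1 − (1 − p)^s for s sessions. For example, at p = 5%: 1 − 0.95^8 = 0.337 and 1 − 0.95^12 = 0.460.

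| Assumed p | Excluded, 8 sessions | Excluded, 12 sessions | Difference (points) | Left of 36: 8 vs 12 |
|---|---|---|---|---|
| 1% | 7.7% | 11.4% | 3.6 | 33.2 vs 31.9 |
| 2% | 14.9% | 21.5% | 6.6 | 30.6 vs 28.2 |
| 3% | 21.6% | 30.6% | 9.0 | 28.2 vs 25.0 |
| 5% | 33.7% | 46.0% | 12.3 | 23.9 vs 19.5 |
| 10% | 57.0% | 71.8% | 14.8 | 15.5 vs 10.2 |

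**When the reserve runs out.** Setting 36(1 − p)^s = 24 gives p = 1 − (24/36)^(1/12) = 3.3% for 12 sessions and p = 1 − (24/36)^(1/8) = 4.9% for 8 sessions.

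**Power of the 12-session arm against sham.** With the retained numbers, a difference of 0.66 and SD 0.608, power is about 98% at p = 2%, 93% at 5% and 73% at 10%.

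**Illustration of bias.** Suppose attenders and excluded participants differ by δ in mean WAS change, by the same amount in each arm, and treatment has no effect. The mean among those retained is then shifted by (share excluded) × δ, and the difference between arms by (difference in shares) × δ. At p = 5% this is 0.123 × 0.5 = 0.062 points for δ = 0.5 (about 9% of 0.66), or 0.123 × 0.2 = 0.025 for δ = 0.2. At p = 2% and δ = 0.5 it is 0.033. These values of δ are assumptions; nothing in the article fixes them or their sign.

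**The case against.** The strongest reply is that the harm is inferred. No attendance, adherence or reaction rate is given. At miss rates of 1% to 3% every arm keeps at least the required 24. At 5% power is still about 93%, and the illustrated bias is small against 0.66. All of this stands. A reader might infer that the arms are shown to be non-comparable, that losses will differ, or that the trial will be underpowered. The documents support none of these as fact. They support only that randomisation no longer guarantees comparability, and that unequal loss is expected if attendance per session is equal.

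Four further limits hold.
- It is tempting to say that each arm has its own selection filter. For attendance that is wrong: the twice-weekly active arm and sham both have 8 sessions. The session-count argument touches only comparisons with the 12-session arm.
- The adverse-event sentence carries the qualifier hypersensitivity, allergies, so reading it as any adverse event stretches it. The shared cream, wipe, film or silicone could cause such reactions under sham too, and people with a history of photosensitivity are screened out. Only reactions to the LED itself are confined to the active arms.
- Only that sentence names the statistical analysis. The attendance and adherence item excludes from the study. Loss from the analysis is the natural reading, since no section keeps those data, but it is a reading. Whether a missed session may be made up is not stated; if it may, the losses above are too high.
- The treating researcher knows the allocation, which might suggest biased exclusions. However, attendance is an objective record, that researcher makes no assessments, and the WAS raters are blinded (section 2.1.5). Only the judgement of who failed to follow advice leaves room for discretion.

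None of this defends the rule. Nor is the point one left to an unseen analysis plan, because the article itself states who is removed. Its promise to describe adverse events keeps them visible but does not restore the randomised comparison.

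**Conclusion.** The point holds in this form. Section 2.1.2 removes participants for events after allocation, explicitly from the analysis for reactions and from the study for missed sessions and non-adherence. The efficacy comparison therefore loses the protection of randomisation. The attendance rule is expected to bear more heavily on the 12-session arm and so on the frequency contrast. The excess exclusion there is 3.6 to 14.8 percentage points over assumed miss rates of 1% to 10%, given independent, equal and unrescheduled misses. The case rests on selection rather than on lost power. The size and direction of the bias cannot be computed from the document and may be modest, but the rule is avoidable and cheap to change.

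**What to change.** Amend section 2.1.2 so that missed sessions, non-adherence and adverse events are no longer reasons for exclusion from the study or the statistical analysis. Keep the existing commitments to describe and treat adverse events.

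State that every randomised participant is analysed in the allocated group for WAS and the other outcomes. Invite all participants to the follow-up assessments already planned (photographs, impressions, FACE-Q), whatever their attendance. After an adverse event, collect outcomes where the investigator judges it feasible. Outcomes that cannot be obtained are then missing data rather than exclusions. Keep the fully attending, event-free set only as a supportive per-protocol analysis, and report adverse events by arm with all treated participants as denominator. This concerns the analysis set and outcome collection, not how treatment is managed.

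The cost is a wording amendment and somewhat more follow-up. The estimate will reflect allocation rather than full adherence and may be diluted. Section 2.1 describes the trial as recruiting, so the change is best made early: follow-up not collected because of exclusion cannot be recovered later.

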#### 2.1.3. Sample size calculation.

The sample size was calculated based on the primary outcome. The outcome considered was the classification of the Lemperle Wrinkle Assessment Scale (WAS).^[29]^ In the study by Sylvie Boisnic,^[30]^ the authors observed that the Lemperle score decreased in both groups after 12 weeks of treatment with a reduction of 1 (±0.7) point in the experimental group and 0.34 (±0.5) point in the placebo group and a statistically significant (*P* < .0002) change from baseline between the 2 groups after 8 weeks of treatment. This study was designed to detect a difference in scores between the groups, considering the mean and standard deviation of the study by Sylvie Boisnic,^[30]^ for the analysis of variance (ANOVA) with 3 groups and repeated measures, with significance level of 5% and power of 95%, with equal allocation for the three groups, requiring 24 participants per group, 72 in total. To control a possible loss, 50% can be added to the sample, with 36 participants per group, that is, 108 in total. The sample calculation was performed using the G-Power Version 3.1.9.4 program (Universität Kiel, Germany).

#### 2.1.4. Randomization.

After completing a questionnaire and being evaluated by the researcher for inclusion and exclusion criteria, a person not involved in the study will randomly distribute the participants among the three experimental groups using an online random sequence generator program (https://www.randomizer.org/tutorial/). After this, opaque envelopes, containing the generated number, will be sealed and will remain in a safe place until participants are recruited for the outpatient clinic. When the participant enters the clinic, the researcher will open the corresponding envelope and begin the specified treatment. Participants will be divided into 3 groups:

(Group 1) Application of PBM twice a week for 4 weeks;

(Group 2) Application of PBM three times a week for 4 weeks;

(Group 3) Application of simulated PBM twice a week for 4 weeks;

#### 2.1.5. Blinding procedures.

The study will be carried out by a research team that will include a researcher who will carry out the application, undergraduate students, and 3 plastic surgeons who will carry out the initial evaluation of the photographs and the reevaluations after the application of the treatment (blind as to the composition of the groups), and a statistician for data processing.

The researcher responsible for the PBM application will pick and open the envelope containing the information of the experimental group in which the participant will be inserted and will proceed with the experiment. A single researcher will carry out the treatment and it will not carry out any type of evaluation. Pre and post-treatment assessments will be made by 3 examiners (3 plastic surgeons) who will not be aware of the group to which each patient will be allocated. Participants will not be aware of whether or not they have received the application of the PBM, as they will be using dark goggles. The person responsible for the application will position the equipment in the irradiation locations in all participants and will only activate the light when provided for in the specific experimental group. In the control group, the mask will be installed and kept off and a white light will be turned on close to the participant’s face so that they have a sensation of luminosity even using the blindfold. The characteristic sound of the device will be triggered by recording in the placebo group for the PBM.

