## Abstract

**Methods and analysis::**

The objective of this study is to compare the effects of PBM with a light-emitting diode mask (660 nm, 6.4 mW/ cm², 8,02 J/ cm², 5.02 mW, 21 minutes) on facial rejuvenation using 2 frequency applications for 4 weeks: one group will receive PBM application on the face, twice a week and another group will receive PBM application 3 times a week. A group with simulated PBM applied twice a week for 4 weeks will be used as a control. The treatment will be performed on female participants aged between 45 and 60 years. After 4 weeks, evaluations of photographic images by specialists (Wrinkle Assessment Scale) as well as the quantitative analysis of the wrinkle size by the Image J software, the depth and width of wrinkles (assessment of face impressions by optical coherence tomography) and the level of Satisfaction with Facial Appearance Overall will be compared with data collected before the start of the study. All data will be analyzed statistically according to their distribution, seeking a level of statistical significance of 0.05.

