Self-assessment has become an important tool to evaluate the results of aesthetic procedures,^[38]^ facial changes resulting from aging can impact the quality of life, self-esteem, social relationships, and activities of individuals. Thus, preventive and corrective interventions are closely related not only to health but also to psychosocial well-being.^[8,9]^ In this sense, the FACE-Q questionnaire, validated for the Portuguese language, will be used to verify the level of satisfaction after treatment.

It is known that most studies that evaluate the face are based on subjective measures (patient satisfaction and photos) or using skin biopsy.^[20]^ The evaluation methods used in this research, are noninvasive, and double-blind and aim to evaluate a set of variables that can be affected or improved by PBM as a result of the frequency of application in the groups. Face photographs will be evaluated by 3 plastic surgeons using the wrinkle scale.^[29]^ These experts will be calibrated for this assessment and must achieve a rate of agreement among peers above 70%. The evaluation of the images by the Image J software, performed by a researcher not involved in this study, aims to bring quantitative data for visual analysis. The researcher will quantify in pixels the wrinkles of interest before and after treatment. The evaluation of wrinkles in plaster casts by OCT is a reliable and accurate method and there are few data in the literature that provide this type of evaluation. Therefore, in addition to contributing as an evaluation in this protocol, it could become a measurement tool in the area of aesthetics.

In summary, this clinical trial aims to contribute to clarifying the role of PBM application frequency in improving the appearance of the facial skin of menopausal women using qualitative and quantitative methodologies.

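### Participant blinding is claimed without limit, but only active light is given three times weekly, so FACE-Q contrasts with that arm are not assuredly participant-blinded

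*Protocol article*

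**What the plan says.** The protocol article randomises to three arms (section 2.1.4): "Application of PBM twice a week for 4 weeks", "Application of PBM three times a week for 4 weeks" and "Application of simulated PBM twice a week for 4 weeks". The abstract gives the same control schedule ("A group with simulated PBM applied twice a week for 4 weeks will be used as a control"), as does section 2.1.6 ("the participants received the simulated application twice a week for 4 weeks"), and the Discussion agrees.

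On blinding, section 2.1.5 says: "Participants will not be aware of whether or not they have received the application of the PBM, as they will be using dark goggles". For the control group it adds a mask that stays off, a white light near the face and a recording of the device's sound. The Discussion describes the trial as double-blind and says of all outcomes together: "The evaluation methods used in this research, are noninvasive, and double-blind".

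FACE-Q (section 2.2.4) is completed by the participant and scored as a sum. Section 2.3 sends numerical variables to repeated measures ANOVA with Tukey comparisons and treats all pairs of arms alike.

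**The concern.** Every masking measure described works inside one session. None hides how often a participant attends, and no extra simulated sessions equalise attendance. The three-times-weekly pattern exists only with real light, so attendance alone can tell an informed participant what she is receiving. For FACE-Q the participant is the assessor, so the blinding of that outcome is the participant's own blinding.

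Comparing application frequencies is the stated purpose of the trial. If FACE-Q favours the three-times-weekly arm, the present text would let that be reported as a double-blind result, although expectation and more contact with the clinic are rival explanations.

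**Working it through.** No stated figure is in dispute; the check sets the schedules against the blinding claim.

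**Inputs.** Schedules are from sections 2.1.4 and 2.1.6. Sample size and equal allocation are from section 2.1.3: 24 per group (24 × 3 = 72), or with the optional 50% addition 24 × 1.5 = 36 per group (36 × 3 = 108). These serve only as head counts; the sample size itself is not affected.

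**1. Sessions per arm** (sessions per week × 4 weeks):

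| Arm | Sessions |
|---|---|
| PBM twice weekly | 2 × 4 = 8 |
| PBM three times weekly | 3 × 4 = 12 |
| Sham twice weekly | 2 × 4 = 8 |

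The three-times-weekly arm has 12 − 8 = 4 more contacts than either other arm, that is 4/8 = 50% more.

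Sections 2.1.4 and 2.1.6 attach the labels group 1 and group 2 to opposite active schedules. That must be reconciled, but it does not alter this check, because sham is twice weekly in both.

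**2. What attendance reveals, under two assumptions about disclosure.** The information given to participants is not shown, so both ends of the range are given.

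- *Participants know the allocation ratio but not which schedules carry sham.* The chance of active light is 72/108 = 2/3 from every participant's viewpoint. Attendance reveals nothing.
- *Participants know the arm schedules.* At three visits a week the chance of active light is 36/36 = 1. At two visits a week it is 36/(36 + 36) = 1/2, in both the active and the sham arm.

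**3. The three FACE-Q contrasts:**

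| Contrast | Gap in inferred chance of active light | Contacts |
|---|---|---|
| Twice-weekly PBM vs sham | 1/2 − 1/2 = 0 | 8 vs 8 |
| Three-times-weekly PBM vs sham | 0 to 1 − 1/2 = 1/2 | 12 vs 8 |
| Three-times vs twice-weekly PBM | 0 to 1 − 1/2 = 1/2 | 12 vs 8 |

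Only the first contrast is balanced whatever participants are told. The second conflicts with the statement in 2.1.5, which concerns real versus simulated light. The third compares two active arms, so it does not contradict that statement directly, but it can carry the same gap in expectation. The contact imbalance in the last two rows does not depend on disclosure.

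**4. Share affected.** One arm of three: 36/108 = 24/72 = 1/3 of participants, and 36/72 = 1/2 of those on active light.

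**5. Other outcomes.** The Wrinkle Assessment Scale, on which the sample size rests, is scored by three surgeons unaware of allocation (2.1.5). The ImageJ evaluator is blind to group (2.2.3). Neither score is supplied by the participant.

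**The case against.** The strongest objection is that inference from attendance requires knowledge the documents do not show participants to have. Section 2.1 says only that the study is explained orally and in writing; the consent text is not shown. This stands. A reader might conclude that participant blinding fails outright in the three-times-weekly arm, but the documents support only the conditional statement. Equally, nothing in the article says that arm schedules are withheld, so the unqualified claim of blinding is not supported either.

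Second, the reach is narrow. The primary outcome and ImageJ are assessed blind to group, and nothing makes the trial's main conclusion depend on FACE-Q. This also stands. A reader might infer that the whole trial, or its primary result, is unblinded; the documents do not support that.

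Third, frequency is the factor under study, and extra contact comes with it unless simulated visits are added. That makes the imbalance a design trade-off and not a misstatement. It does not make a FACE-Q difference attributable to light alone.

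Fourth, one might want the participant information reworded. The present wording is not available, so there is no ground for saying it needs change, and altering it in a trial already recruiting could leave earlier and later participants with different disclosure.

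**Conclusion.** The concern holds in a limited form. Section 2.1.5 and the Discussion claim participant blinding and double-blind evaluation without limit; the design secures this for FACE-Q only in twice-weekly PBM versus twice-weekly sham. Three-times-weekly PBM versus sham is in direct tension with the claim, and three-times versus twice-weekly may carry an imbalance in expectation and contact.

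The size is one arm of three, two of three pairwise contrasts and one self-reported outcome. The possible gap in inferred chance of active light runs from 0 to 1/2, depending on what participants know of the arm schedules; the difference of 12 versus 8 contacts holds regardless. How far either would move the FACE-Q score cannot be derived from the documents. An analysis plan could label these contrasts properly but could not restore the blinding.

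**What to change.** - **Section 2.1.5 and the Discussion:** limit the participant-blinding statement to twice-weekly PBM versus twice-weekly sham, and stop describing all evaluation methods as double-blind without excepting the FACE-Q contrasts that involve the three-times-weekly arm.
- **Section 2.3:** make twice-weekly PBM versus sham the FACE-Q contrast from which a blinded efficacy conclusion is drawn. Report FACE-Q contrasts with the three-times-weekly arm as not assuredly participant-blinded, and do not base the frequency conclusion on them.
- **Optional:** add one end-of-study question asking which treatment the participant believes she received, and report the answers by arm. Participants who have already finished would be missing from it.

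The cost is a change of protocol wording and a weaker FACE-Q claim for the three-times-weekly arm. Arms, schedules, sample size and participant information stay as they are.
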